### Intervention

The treatment will encompass 30 sessions of either lDLPFC iTBS or sham iTBS over 6 weeks (5 sessions per week, daily from Monday to Friday). All treatment sessions will be performed in person at the respective treatment sites by assistant medical technicians, post-graduate psychologists, research assistants, and medical students under the supervision of a medical doctor. All TMS operators will receive sufficient on-site training for conducting the treatment. During the session, patients will be seated in comfortable chairs in a neutral-colored room. No other patients or personnel will be present except for the operators, who will be instructed not to converse with the participant during stimulation. Patients will wear hearing protection during stimulation.

Active iTBS treatment will follow the original protocol by Huang et al. [27] except for using 80% resting motor threshold (rMT) instead of active motor threshold (aMT), but also comprising bursts of 3 pulses at 50 Hz repeated at 200 ms intervals (5 Hz), with an intertrain interval of 8 s, for a total of 600 stimuli (i.e. lasting about 3 min). In a recent study, we characterized the neural response to this iTBS protocol applied over the left DLPFC using interleaved TMS-fMRI [28]. The individual rMT will be determined as the lowest stimulation intensity that elicits motor-evoked potentials (MEPs) with a minimum amplitude of 0.050 mV from the relaxed abductor pollicis brevis muscles in at least 5 out of 10 stimulations of the left motor hotspot region (M1 hand). The individual lDLPFC will be located according to the established Beam F3 method [29]. Motor threshold determination and active and sham iTBS will be performed using the PowerMag Clinical 100 stimulator (Mag & More GmbH, Munich, Germany) with a marked “PMD70-PCOOL” for threshold determination, a separate, unmarked “PMD70-PCOOL” for active iTBS, and an unmarked “PMD70-PCOOL-SHAM” coil for sham iTBS. The manufacturers were not involved in the study design and will not be involved in collecting data, analyzing data, interpreting data, or writing the report. Modifications to the outlined treatment protocol will not be allowed.

During the 6 week treatment phase, concurrent standard psychotherapeutic and psychosocial interventions will be allowed, but psychoactive pharmacotherapy, except for pre-defined on-demand medication, will not be allowed. On-demand medication will include zopiclone (up to 7.5 mg/day orally), benzodiazepines up to a dose equivalent to Lorazepam 1.0 mg/day orally, quetiapine up to a dose of 50 mg/day orally, promethazine up to a dose of 50 mg/day orally, as well as ibuprofen, Paracetamol, ASA for treatment of local pain, dental pain or headaches, as necessary. During follow-up, we will observe patients under naturalistic conditions without interfering with their treatment.

## Measures

Table 1 presents an overview of measures that are assessed in this trial.

**Table 1 Tab1:** Schedule of visits

Visit	Pre-treatment		Treatment			Follow-up	
	Screen	Baseline	V10	V20	V30	FU1	FU2
Week	− 2 to 0		2	4	6	12	24
Screening assessments							
DIPS	x						
Medical and psychiatric history	x						
Sociodemographic information	x						
APA screener	x				x	x	x
BSL-23	x				x	x	x
Outcome assessments							
MADRS		x	x	x	x	x	x
DASS-21		x	x	x	x	x	x
DARS		x	x	x	x	x	x
WHO-DAS 2.0		x			x	x	x
Exploratory assessments							
ISI		x			x	x	x
CTQ		x			x	x	x
PID5BF + M		x			x	x	x
SNI		x			x	x	x
UCLA		x			x	x	x
RSQ		x			x	x	x
Safety assessments							
C-SSRS	x	x	x	x	x		
Physical exam	x				x		
Vital signs	x				x		
Urine HCG*	x						
Treatment-related assessments							
Blinding check			x	x	x		
CEQ		x	x	x	x		
Optional assessments							
MRI		x			x	x	

*Women only

DIPS, Diagnostisches Interview bei psychischen Störungen; APA screener, DSM-5 self-rated level 1 cross-cutting symptom measure—adult version; BSL-23, Borderline Symptom List, 23-item version; MADRS, Montgomery-Åsberg Depression Rating Scale; DASS-21, Depression, Anxiety, and Stress Scale, 21-item version; DARS, Dimensional Anhedonia Rating Scale; WHO-DAS 2.0. World Health Organisation Disability Assessment Schedule (WHODAS 2.0) self-report version; ISI, Insomnia Severity Index; CTQ, Childhood Trauma Questionnaire; PID5BF + M, Persönlichkeitsinventar für DSM-5 und ICD-11—Kurzform Modifiziert; SNI, Social Network Index; UCLA, UCLA Loneliness Scale; RSQ, Rejection Sensitivity Questionnaire; C-SSRS, Columbia-Suicide Severity Rating Scale; CEQ, Credibility/Expectancy Questionnaire; MRI, Magnetic resonance imaging

### Primary outcome

The primary outcome will be the difference in MADRS scores at week 6 (post-treatment visit) between active iTBS and sham iTBS, controlling for baseline MADRS scores. The MADRS is a clinician-rated measure of depression severity that assesses ten common depressive symptoms (apparent sadness, reported sadness, inner tension, reduced sleep, reduced appetite, concentration difficulties, lassitude, inability to feel, pessimistic thoughts, and suicidal thoughts) on a scale from 0–6. The overall score ranges from 0 to 60, with higher MADRS scores indicating more severe depression. We will use the structured interview guide for the MADRS (SIGMA)[30] to improve the reliability of assessments between study raters. All raters will receive video-based SIGMA training, during which they will rate two example video interviews.

### Secondary, exploratory outcomes

Secondary outcomes will explore group differences in (1) MADRS score changes from baseline to 3 and 6 months; (2) response rates (≥ 50% MADRS score reduction) at week 6, and 3 and 6 months; (3) remission rates (MADRS score ≤ 10) at week 6, and 3 and 6 months; (4) changes in self-reported depression, anxiety, and stress using the Depression, Anxiety, and Stress Scale, 21-item version (DASS-21)[31] at week 6, and 3 and 6 months; (5) the change of self-reported anhedonia using the Dimensional Anhedonia Rating Scale (DARS) [32] at week 6, and 3 and 6 months; and (6) change of self-reported health-related functioning using the World Health Organisation Disability Assessment Schedule (WHODAS 2.0) [33] at week 6, and 3 and 6 months.

### Safety and tolerability outcomes

Safety outcomes will be the group differences in (1) rates of reported adverse events (AEs); (2) change of vital signs (blood pressure and heart rate) and Body Mass Index (BMI); and (3) rates of reported instances of suicidality; all measured at week 6 (post-treatment visit). Suicidality will be assessed at every visit using the Columbia-Suicide Severity Rating Scale (C-SSRS) [34], an interviewer-rated scale that measures the current intensity of patients’ specific suicidal ideation on the day of assessment. A patient will be identified as experiencing acute suicidality if they affirm item 4, item 5, or both. Upon such identification, treatment will be halted immediately, and the patient will be directed to suitable crisis intervention services for urgent care. Tolerability outcomes will be the group differences in (1) rates of participants who discontinue the treatment; and (2) rates of participants who discontinue the treatment due to an AE.

### Other assessments

The following variables and measures will be collected at baseline and/or during the course of the trial as potential moderators and mediators of treatment: Demographic and clinical variables (e.g., age and gender, prior psychiatric treatment, medical co-morbidities); self-reported symptoms of insomnia using the Insomnia severity index (ISI) [35]; self-reported experiences of adverse childhood experiences using the Childhood Trauma Questionnaire (CTQ) [36]; self-reported maladaptive personality traits, using the PID5BF + M, a validated, expanded German version of the Personality Inventory for DSM-5 (PID-5) [37]; self-reported participation in social relationships using the Social Network Index (SNI) [38]; self-reported loneliness using the UCLA Loneliness Scale (UCLA) [39]; rejection sensitivity using the Rejection Sensitivity Questionnaire (RSQ) [40]; and outcome expectation beliefs using the Credibility/Expectancy Questionnaire (CEQ) [41]. We will explore participants' beliefs about their intervention allocation by asking them to guess their assigned treatment condition, rate their confidence in this guess, and provide potential reasons for their guess at weeks 2, 4, and 6 (post-treatment) using a custom-designed questionnaire.

Furthermore, participants will be asked to participate in optional, exploratory MRI assessments prior to treatment (mri_t0; additional MRI sequences will be added to the mandatory safety measurement), within two weeks after the end of treatment (mri_t1), and 3 months after randomization (mri_t2). MRI data will be used to explore potential longitudinal effects of iTBS on brain anatomy and functioning, identify potential moderators of treatment response, and investigate dose–response relationships using electric-field modeling. Imaging sequences will encompass anatomical (such as T1-weighted and T2-weighted structural sequences, diffusion tensor imaging, DTI) and functional scans during resting state (rsfMRI). Participants will receive a reimbursement of 50 € per MRI assessment.

### Statistical methods and analysis

This protocol pre-specifies only the primary sequential analyses; others are exploratory. Safety assessments will be descriptive. All analyses will be conducted in R [42]. The analysis scripts are available at 10.17605/OSF.IO/B397U.

Following the methodology of Blackwell et al. [15], we will employ sequential analyses (see Fig. 3) with directional Bayes factors (BFs) to assess the efficacy of active and sham iTBS on the primary outcome. BFs [43] essentially calculate the probability of the observed data under the alternative hypothesis (active iTBS reduces MADRS scores more than sham) divided by the probability of the observed data under the null hypothesis (no superiority of active iTBS). The progression of the trial depends on pre-defined parameters: the minimal sample size per arm, N_min_, at which sequential analyses are initiated; a maximum sample size, N_max_; a BF threshold indicating lack of superiority, BF_fail_; and a BF threshold indicating superiority, BF_success_. The specific parameter set was determined by simulation (see below). The trial will halt upon reaching any threshold or N_max_. In the latter case, discussions on extending recruitment may occur with the funder, pending additional ethical approval. Participants ongoing in treatment at trial cessation will complete it, with their data included in final analyses but not in further sequential analyses.

**Fig. 3 Fig3:**
[figure not shown]
Sequential Bayesian analysis design

Analyses will follow an intention-to-treat approach, including all participants randomized to a condition, irrespective of intervention completion or outcome data availability. For sensitivity analyses, participants will be classified as per protocol if they complete the 6-week treatment period and receive at least 20 treatment sessions within six weeks. Sequential analyses will commence once each arm meets the predefined minimum sample size N_min_. Analyses will be updated with each participant’s trial completion. Following Blackwell et al. (2022), missing data will be handled using constrained longitudinal data analysis (cLDA) via the R package nlme [44]. Bayes factors will be estimated with the R package BayesFactor [45] using the t-statistic for the Time x Group interaction and directional default Cauchy prior (rscale parameter = √2/2). Effect sizes (adjusted Cohen's d) and estimated means for the primary outcome, along with their 95% confidence intervals (CIs), will be derived from the cLDA model using the R packages effectsize [46] and emmeans [47]. Analyses will be performed by a statistician ([name]) aware of participant allocation (given the directional nature of the analyses), sharing results with the research team only if a BF boundary is met or after N_max_ is reached.

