### Sample size calculation

Using pairwise comparison simulations, we set analysis parameters to achieve a false-positive rate of < 5% and a power of ~ 80% for detecting an effect size of d = 0.6. The choice of effect size was revised after the trial commenced but prior to the start of sequential analysis, based on a recent meta-analysis of iTBS [48]. Initially, we selected an effect-size of 0.8 due to practical considerations, including the absence of specific evidence for iTBS in younger populations and constraints on trial funding. For N_min_ = 26; N_max_ = 45; BF_fail_ = 1/5; and BF_success_ = 5, simulations with up to 15% missing data suggest that these parameters provide a < 5% false-positive rate and 71.35% power to reach the BF_fail_ threshold before recruitment of N_max_ when d = 0; and 81% power to hit BF_success_ before N_max_ for an effect size of d = 0.6(see Table 2). For practical purposes, N_max_ will be operationalized on the basis of the total sample size, that is, when the total number of participants randomized is 2 × N_max_ (i.e., *N* = 90), regardless of the distribution across arms. Simulation scripts and results of the initial and revised sample size calculations are available at 10.17605/OSF.IO/B397U.

**Table 2 Tab2:** Pairwise comparison simulations using cLDA

	Probability of hitting BF threshold at each participant number (per group)									
	Hit BFfail					Hit BFsuccess				
d	26	30	35	40	45	26	30	35	40	45
− 0.2	73.85	82.45	87.20	90.90	93.40	0.20	0.45	0.45	0.70	0.70
0	46.20	55.60	62.05	67.20	71.35	**1.30**	**1.95**	**2.45**	**2.75**	**3.00**
0.2	18.85	25.15	30.15	33.40	35.40	6.20	9.95	13.10	15.75	17.95
0.3	11.45	15.90	18.65	20.40	22.10	12.85	18.05	22.25	26.50	29.55
0.4	5.45	7.25	8.55	9.70	10.15	21.85	31.10	37.55	42.75	47.45
0.51	2.00	2.95	3.40	3.85	4.00	34.65	45.60	54.10	60.25	66.55
0.6	1.25	1.55	1.85	1.95	2.00	**48.95**	**60.25**	**69.45**	**76.25**	**81.15**
0.71	0.30	0.50	0.55	0.55	0.55	63.10	74.65	82.55	87.15	91.10
0.8	0.05	0.20	0.20	0.20	0.20	74.15	83.35	89.80	92.65	95.35

Bold values indicate false-positive rate and power estimates for an effect size of 0.6

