Simulations for the following parameters: N_min_ = 26, N_max_ = 45, BF_fail_ = 1/5, BF_success_ = 5; 15% missing data. Simulations were conducted in RStudio running R version 4.2.2, using 2000 simulations. Estimated effect sizes (d) are a form of Cohen’s d estimated from a t-test on the change scores between groups, with positive d values indicating superiority of the treatment condition to the sham condition. Although d values at intervals of 0.1 were simulated (e.g. 0.2, 0.3, 0.4), the table presents the mean observed effect size across the simulations, which often deviate slightly from these values.

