Acknowledging the heterogenous and evolving clinical manifestation in young patients [49] and based on meta-analytic evidence for the efficacy of left DLPFC rTMS in depressive syndromes across a transdiagnostic spectrum [7], our study includes adolescents and young adults with MDD, PDD, and BD and allows for pertinent comorbidities, except where such conditions likely disrupt trial procedures (e.g., mania, severe borderline psychopathology) or where alternative treatments are required (e.g., obsessive–compulsive disorder). In contrast to RCTs in adults that advocate for accelerated or high-intensity iTBS protocols to mitigate depressive symptoms [50], we opted for a standard iTBS variant only minimally modified from the original Huang et al. [27] protocol and will apply this protocol for 30 sessions within six weeks. This choice is based on the efficacy of a longer iTBS treatment duration in adults demonstrated in multicenter trials [5], recent trials indicating limited efficacy of shorter treatment protocols (i.e. only 10 sessions within two weeks) in younger patients [13], and target involvement by this protocol as shown in a recent interleaved TMS-fMRI study [28]. Moving away from the usual heuristic selection of treatment parameters in treatment development research, our trial employs a sequential Bayesian design that can be later expanded into an adaptive multiarm leapfrog trial allowing for ongoing refinements of the treatment protocol. Specifically, if the active iTBS group reaches the superiority threshold (BF_success_), it replaces the sham group as the comparison arm. New treatment arms with novel rTMS targets and protocols could then be added and tested within a running platform trial. These arms can be informed by emerging clinical evidence (e.g., introducing bilateral or accelerated stimulation based on results from ongoing trials [51, 52]), participant feedback (e.g. reducing the number of stimulation sessions to minimize attrition), or secondary analyses of current trial data (e.g., shortening the treatment duration if improvement plateaus are observed in the active iTBS group). Using a leapfrog rolling design, each active comparison arm can subsequently be superseded by new arms that demonstrate superiority, while underperforming arms exit the trial. This frees up resources to either introduce alternative treatment settings or concentrate efforts on existing arms. This iterative process continues until researchers determine that an optimized intervention is ready for large-scale confirmatory trials, or it can be perpetually embedded in routine practice as a platform for continually testing new ideas. Compared to traditional treatment development, which typically involves series of small, sham-controlled studies, this approach reduces required sample sizes, minimizes exposure to sham treatments or ineffective versions of the intervention, and rapidly incorporates new knowledge within an existing trial infrastructure, without the need to setup separate parallel trials. Thus, this pilot trial represents the initial phase in a translational framework aimed at systematically optimizing promising treatment modalities prior to launching more resource-intensive confirmatory multicenter trials.

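### The effect size and 95% CI come from the ordinary cLDA model with no allowance for sequential stopping; after a stop for success the estimate is on average about 18–20% too high at a true d of 0.6

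*Protocol article*

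**What the plan says.** All of this is in the protocol article, under Statistical methods and analysis and Sample size calculation.

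- **Decision statistic.** The Bayes factor is computed "using the t-statistic for the Time x Group interaction and directional default Cauchy prior", with scale √2/2.
- **Looks.** Once each arm has reached the minimum, "Analyses will be updated with each participant" who completes the trial. The trial halts at either boundary or at the maximum sample size.
- **Boundaries.** "For N_min_ = 26; N_max_ = 45; BF_fail_ = 1/5; and BF_success_ = 5, simulations with up to 15% missing data" are the basis of Table 2. The targets are a false-positive rate below 5% and "a power of ~ 80% for detecting an effect size of d = 0.6". The table reports 3.00% and 81.15% at 45 per arm.
- **Estimate.** Adjusted Cohen's d and "estimated means for the primary outcome, along with their 95% confidence intervals (CIs), will be derived from the cLDA model" through standard R packages.
- **Overrun.** Patients in treatment when the trial stops finish their course and enter the final analysis, but no further sequential look.

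Table 2 gives only the probability of reaching each boundary. Its d is "a form of Cohen’s d estimated from a t-test on the change scores between groups". Nothing in the article describes the behaviour of the estimate or interval after a stop.

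**The concern.** A boundary on the t-statistic lets the trial stop for success only when the current estimate is high enough. An ordinary model estimate reported after such a stop is therefore selected upwards, and its confidence interval is built as if the sample size had been fixed. The design was simulated for its decision but, as reported, not for its estimate.

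The article presents this pilot as a first step towards later platform and confirmatory trials, where an effect estimate is a natural planning input. As an illustration, take a two-sample t-test at two-sided 5% with 80% target power. Planning on d = 0.72 gives 32 per arm. If the truth is 0.6, that trial has about 66% power, and 45 per arm would be needed. Planning on 0.65 gives 39 per arm. If the truth is 0.4, power is about 41%, and 100 per arm would be needed.

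**Working it through.** **Inputs from the article:** 1:1 allocation; 26 to 45 per arm; Bayes-factor boundaries 1/5 and 5; half-Cauchy prior with scale 0.707; 15% missing; d on the change-score scale.

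**Assumptions:** pre-post correlation ρ = 0.5 (not in the article; it reproduces Table 2); a baseline-adjusted analysis standing in for the two-timepoint cLDA; one look per n per arm. For the overrun, 90 patients over about 36 months is 2.5 per month. Over six weeks (about 1.4 months) that makes 3 to 4 patients in treatment, or about 2 per arm.

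**Hand check at the first look.** With n = 26 per arm, a Bayes factor of 5 corresponds to t = 2.349.

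- Outcomes per arm: 26 × 0.85 = 22.1.
- Standard error of d: √((1+ρ)/2) × √(2/22.1) = 0.866 × 0.3008 = 0.2605.
- Estimate needed to stop for success: about 2.349 × 0.2605 = 0.61, already above the design value of 0.6.
- Chance of success at d = 0.6: Φ(0.6/0.2605 − 2.349) = Φ(−0.046) = 48.2%. Table 2 gives 48.95%.
- Mean estimate in those trials: 0.6 + 0.2605 × φ(0.046)/0.482 = 0.6 + 0.2605 × 0.827 = 0.82, which is +36%.

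**Full sequence by simulation.** Table 2 is reproduced on the success side: 3.0% at d = 0 (stated 3.00%) and 80.6–81.3% at d = 0.6 (stated 81.15%). Success here means crossing at any look from 26 to 45 per arm.

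| True d | Success, Table 2 / simulated | Mean estimate given success | Bias given success | Same, 2 overrun per arm | Bias, all trials | CI coverage given success | CI coverage, all trials |
|---|---|---|---|---|---|---|---|
| 0.2 | 17.95 / 16.5% | 0.61 | +202% | +192% | −4% | 85% | 95% |
| 0.3 | 29.55 / 30.2% | 0.62 | +107% | +100% | +5% | 92% | 95% |
| 0.4 | 47.45 / 47.9% | 0.65 | +61% | +56% | +8% | 95% | 93% |
| 0.51 | 66.55 / 68.2% | 0.68 | +32% | +31% | +8% | 96% | 94% |
| 0.6 | 81.15 / 81.3% | 0.72 | +19% | +18% | +7% | 97% | 95% |
| 0.8 | 95.35 / 96.6% | 0.84 | +5% | +5% | +3% | 97% | 96% |

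Counting only successes before the maximum sample size gives +20% at 0.6 and +62% at 0.4. The excess arises mainly at the first look: at d = 0.6, stops at n = 26 average +36% and stops at n = 27 to 44 average −3%. With overrun, the all-trials bias at 0.6 is about +6%.

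**Sensitivity at d = 0.6, success before the maximum:** +15% with ρ = 0.3, +25% with ρ = 0.7, and +31% with an unadjusted change-score t-test.

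**A mismatch to note.** The failure side is not matched with n per arm in the Bayes factor: 57.6% at d = 0, against 71.35% in Table 2. Doubling n in the Bayes factor gives 73.0% and leaves the bias on success at +20%.

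**The case against.** **Most of the bias is not specific to sequential stopping.** Any trial read only when it succeeds overstates its effect. Single-look trials of the same kind, read only on two-sided p < 0.05 favouring active, give:

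| True d | Sequential | Fixed 26 per arm | Fixed 36 | Fixed 45 |
|---|---|---|---|---|
| 0.6 | +19% | +27% | +15% | +9% |
| 0.4 | +61% | +72% | +51% | +39% |

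This stands. The excess over a fixed trial is about 4–10 points at 36 per arm and 10–22 points at 45, and a fixed trial at 26 per arm is worse than the planned design. So the whole 18–20% or 55–60% cannot be charged to the stopping rule.

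**The interval is largely sound.** A reader might infer that the 95% CI is invalid. Overall coverage of 93–96%, and 95–97% given success at d of 0.4 to 0.6, do not support that. Coverage falls clearly only given success with a true d of 0.3 or less.

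**The estimate does not drive the next step.** A reader might infer that an inflated d would promote the arm or size the next trial. The Discussion says that "if the active iTBS group reaches the superiority threshold (BF_success_), it replaces the sham group as the comparison arm"; promotion rests on the Bayes factor. No section says this pilot's d will set a later sample size, and further optimisation is placed before any confirmatory trial. The planning figures above are therefore a conditional illustration.

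**Adjusted estimates may sit elsewhere.** The linked analysis and simulation scripts, and any statistical analysis plan, were not available. But the article itself fixes the estimator and interval, so a note on how to read them belongs with it.

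**Conclusion.** The point holds as a modest one about estimation and reporting. The article fixes an ordinary cLDA estimate and CI after a data-dependent stop and says nothing of the selection. Given a stop for success, the estimate is on average about 18–20% too high at a true d of 0.6, about 55–60% at 0.4 and about 5% at 0.8. These figures assume a correlation of 0.5 and 15% missing data; the lower ends include about two overrun patients per arm.

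It would be wrong to say that the trial's result will be overstated by 20–60%. That range applies only given success and only for true effects of about 0.4 to 0.6. Over all trials the bias is about 6–7% at d = 0.6. Nor is the estimate simply the one at the boundary crossing, because the overrun data enter the final analysis and trim the bias by up to about 5 points in that range. The decision rule and its simulated 3% false-positive rate are untouched.

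**What to change.** 1. Keep the cLDA effect size and CI, and label them *unadjusted for sequential stopping*.
2. Report beside them either a stopping-bias-adjusted estimate from the existing simulation, with overrun patients included, or a posterior estimate under a two-sided Cauchy prior. If the simulation route is taken, state in advance whether the correction averages over all outcomes or conditions on success. The two differ (about +7% against +19% at d = 0.6). The conditional form is also unstable, because even true-null trials that succeed report a mean d of about 0.60.
3. Do not make the posterior under the half-Cauchy prior the main estimate. That prior allows only positive effects, so its interval could never include zero or harm, even after a stop for failure. It also corrects little: an observed 0.81 at 26 per arm becomes 0.71.
4. Add mean estimate and CI coverage at stopping to the simulation table, by true d.

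The cost is a few lines of code and a somewhat smaller reported effect after an early success. Enrolment, boundaries and conduct do not change. The article reports one participant enrolled and an amendment on sample size in preparation, so the addition could go into that amendment.

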## Abstract

Intermittent theta burst stimulation (iTBS), a variant of repetitive transcranial magnetic stimulation (rTMS), is an established treatment for adults with major depressive disorder (MDD). Due to its favorable safety profile, iTBS is also a promising early intervention in the transition phase from adolescence to early adulthood, but this has not been systematically investigated to date. Thus, the EARLY-BURST trial investigates the efficacy and safety of iTBS over the left dorsolateral prefrontal cortex (lDLPFC) in treatment-seeking young patients (age 16–26 years) with depressive disorders (i.e. major depressive disorder, persistent depressive disorder, bipolar depression), allowing for relevant co-morbidities. Participants have not received antidepressant or antipsychotic medication during the last 12 months except for short-term (< 2 weeks) on-demand medication. The trial will employ a novel sequential Bayesian, randomized, double-blind, parallel-group, sham-controlled design. Up to 90 patients at two clinical sites (Munich, Augsburg) will be randomized 1:1 to the treatment groups, with sequential analyses starting after 26 patients in each group completed the treatment. The primary outcome will be the difference in depression severity at week 6 (post-treatment visit) between active iTBS and sham iTBS, assessed with the Montgomery-Åsberg Depression Rating Scale (MADRS). The trial is planned to be expanded towards a three-arm leapfrog design, contingent on securing additional funding. Thus, in addition to potentially providing evidence of iTBS’s efficacy in adolescents and young adults with depressive disorders, the EARLY-BURST trial aims at setting the stage for subsequent platform trials in this dynamic research field, where novel adaptive study designs are required to meet the need for rapidly testing promising new vs established rTMS protocols.

*Trial registration:* DRKS00033313.

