
### Randomization, assignment concealment, and blinding

Eligible patients will be randomized 1:1 to the active iTBS or sham iTBS treatment arms. An independent statistician ([name]) will do the randomization, using an in-house R script (with random sequences from random.org) to generate randomly permuted blocks of varying lengths, stratified by study sites (LMU University Hospital vs. University of Augsburg) and biological sex at birth. After baseline assessments, clinical raters will provide participant stratification information to [name]. [name] will then send one of two non-descriptive, alphanumeric codes via mail to the TMS operators, matching markings on either the active iTBS or sham iTBS coil. The markings will be applied by an independent clinician not involved in the administration, recruitment, treatment, medical oversight, analysis, or any other study-related procedure prior to the study initiation. Apart from the non-descriptive markings, the sham coils look identical to the active stimulation coils, generate identical sounds, and have similar weights. Furthermore, they emit minimal magnetic field strengths with which only the nearest area (such as the scalp) is stimulated, producing a twitching sensation without neural activity. Thus, operators will be able to select the correct coil while remaining blinded to the treatment condition. Study raters will not be involved in the treatment sessions and thus will be kept blinded. Treatment conditions will be revealed after the final study analysis has been conducted.

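### The release rule lets group results reach the research team while some week-6 and many follow-up MADRS ratings are still to be made

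*Protocol article*

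**What the plan says.** The release rule stands in the protocol article under Statistical methods and analysis, in the text after Fig. 3. The statistician who runs the sequential analyses knows the allocation and works under the condition of "sharing results with the research team only if a BF boundary is met or after N_max_ is reached". No later milestone is named.

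Four other statements bear on it:

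- Statistical methods and analysis: "The trial will halt upon reaching any threshold or N_max". For patients in the pipeline: "Participants ongoing in treatment at trial cessation will complete it, with their data included in final analyses but not in further sequential analyses".
- Sample size calculation: the maximum is operationalised as the point "when the total number of participants randomized is 2 × N_max", that is 90 patients randomised, not 90 patients rated.
- Statistical methods and analysis: at the maximum, "discussions on extending recruitment may occur with the funder", subject to further ethical approval. The Discussion links such talks to promising preliminary results.
- Randomization, assignment concealment, and blinding: raters stay away from treatment sessions, and "Treatment conditions will be revealed after the final study analysis has been conducted".

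Under Primary outcome, "The MADRS is a clinician-rated measure of depression severity". Table 1 schedules it at weeks 6, 12 and 24. The week-12 and week-24 scores feed the secondary change, response and remission outcomes.

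**The concern.** The stop of the trial and the end of outcome assessment are different dates, and the release rule is tied to the first. At a boundary crossing, patients in treatment still have their week-6 rating ahead of them. At the maximum, the 90th patient has only just been randomised. In both cases recent participants also await weeks 12 and 24.

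The two stated safeguards, raters absent from sessions and codes held back until the final analysis, protect individual allocation. Neither withholds the group result, and nothing in the article places raters or operators outside the research team. A rater who knows that active stimulation succeeded or failed may score a clinician-rated scale with that in mind. If recruitment were then extended, the same team could be recruiting, treating and rating with the results known.

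**Working it through.** **1. The plan's own figure.** 2 × N_max = 2 × 45 = 90 randomised, as stated.

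**2. Order of events.** The first analysis comes "with sequential analyses starting after 26 patients in each group completed the treatment", so each sequential look uses completed week-6 data while later patients are still in treatment. A crossing halts the trial, the remaining patients complete treatment, and their data enter the final analysis. The earliest permitted release (crossing or maximum) therefore precedes the final analysis.

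**3. Ratings outstanding at the stop.** Inputs: up to 90 patients; recruitment April 2024 to April 2027, about 36 months; ratings at weeks 6, 12 and 24 (Trial design; Table 1). Uniform accrual is my assumption.

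Formula: patients with a rating outstanding = accrual per week × weeks to that rating.

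- 36 months = 36 × 30.44 / 7 = 156.5 weeks, and 90 / 156.5 = 0.575 per week (2.5 per month).
- Before week 6: 0.575 × 6 = 3.4 to 3.5.
- Between weeks 6 and 24: 0.575 × 18 = 10.3.
- Week-24 rating outstanding: 0.575 × 24 = 13.8, about 14.

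Sensitivity to the accrual rate:

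| Accrual | Before week 6 | Weeks 6 to 24 | Total |
|---|---|---|---|
| 52 in 36 months | 2.0 | 6.0 | about 8 |
| 90 in 36 months | 3.4 | 10.3 | about 14 |
| 90 in 30 months | 4.1 | 12.4 | about 17 |

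**4. As shares.** At the earliest stop about 52 + 3.5, or roughly 56, are randomised.

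- Week 6: 3.5 / 56 = about 6% at the earliest stop, and 3.5 / 90 = about 4% at the maximum.
- Week 24: 14 / 56 = 25%, and 14 / 90 = about 15 to 16%.

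If release at the maximum waited for the 90th patient's week-6 rating, no primary rating would be pending, but about 10 patients would still await week 24.

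**5. How often an early stop occurs (Table 2).** A boundary is hit at 26 per group with probability 46.20 + 1.30 = 47.5% at d = 0 and 1.25 + 48.95 = 50.2% at d = 0.6. The earliest stop, where the exposed share is largest, is thus a common outcome.

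**6. How often the maximum is reached undecided (Table 2, 45 per group).** Formula: 100 − BF_fail − BF_success.

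- d = 0: 100 − 71.35 − 3.00 = 25.65%
- d = 0.3: 100 − 22.10 − 29.55 = 48.35%
- d = 0.6: 100 − 2.00 − 81.15 = 16.85%

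These are shares of trials in which an extension could be discussed. They are not probabilities of an extension.

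**The case against.** Several points against the concern are sound.

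- **Timing.** A reader might infer that results are released the moment a boundary is crossed. The text does not say so. It sets the earliest permitted time. It also imposes no wait.
- **Recipients.** A reader might infer that raters and operators are told. The article does not define the research team and says that raters are kept blinded, so release to non-rating investigators only would be consistent with it. The full protocol may say who receives what. What can be said is that the stated rule does not exclude raters or operators.
- **Unblinding.** A reader might see a contradiction with the statement on revealing treatment conditions. There is none: that statement concerns allocation, the release rule concerns group results. A rater who knows which arm did better but not who is in it has no direct basis for scoring the arms differently, and a general shift would affect both. Bias in the contrast needs a guess at allocation. Such a guess is conceivable, because operators work with two codes matched to coil markings and can see which patients share a coil, but that step is inference.
- **The sequential decision.** A reader might infer that the error rates in Table 2 are compromised. They are not. Ratings behind a crossing were made before any release, and later data enter no further sequential analysis.
- **Weight of the exposed outcomes.** The follow-up outcomes are labelled exploratory and are observed under naturalistic treatment.
- **Extension.** It is conditional, needs ethical approval, and its dependence on promising results is disclosed as part of a stated limitation.

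These points limit the size of the problem. They do not supply the missing delay or the missing separation between those who know the result and those who still rate.

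**Conclusion.** The point holds in a limited form. As written, the rule allows group results to be shared before about 3 to 4 week-6 ratings (about 4 to 6% of those randomised) and before the week-24 rating of about 14 participants (range about 8 to 17). Individual allocation remains masked and a boundary decision stands.

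The risk is expectation bias in three places: the final week-6 estimate, where it is probably small; the exploratory week-12 and week-24 MADRS, response and remission outcomes, where more ratings are exposed; and any extension conducted by staff who know the results. The counts rest on uniform accrual. The size of any bias cannot be derived from the article. The change is worth making because it is cheap, not because the primary inference is in danger.

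**What to change.** Change the release rule as follows:

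1. At a crossing or at N_max, the statistician reports only that recruitment stops, without the boundary, Bayes factor or group means.
2. Group results go to the research team after the last randomised participant's week-6 MADRS is entered and locked.
3. MADRS raters and TMS operators who still assess or treat participants are not told group results until they have finished; for raters this means the last FU2.
4. If an extension is considered, results go to the funder in a closed report and not to those who recruit, treat or rate.

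**Cost.** Results reach the team about 6 weeks later and raters up to about 24 weeks later. The same 6 weeks would delay any move to the multi-arm design that the Discussion foresees after success. A small firewall has to be maintained between informed investigators and raters. Stopping thresholds, sample size and analysis model do not change. The article reports one participant enrolled and an ethics amendment in preparation, so the rule could be added before any result exists.
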